## Abstract

**Introduction:**

Childhood cancer affects approximately 600,000 children and adolescents worldwide, and chemotherapy is the main form of treatment. However, chemotherapy treatment causes feelings of fear and anxiety especially in the patient’s caregiver. Thus, strategies that help the health education process directed towards caregivers are essential for strengthening knowledge and reducing anxiety involved with the beginning of treatment.

**Objective:**

To present a study protocol to evaluate the effect of a multimedia strategy compared to standard guidelines for acquiring knowledge and reducing anxiety among caregivers of children and adolescents with cancer undergoing chemotherapy.

**Methods:**

A randomized, controlled, single-blind, two-armed clinical trial will be carried out. Fifty-two caregivers of children and adolescents who will start chemotherapy will participate in the study, which will be randomly assigned into Experimental Group, which involves the evaluation of the effect of a multimedia strategy composed of a digital animation film about the chemotherapy process, used as tool for health education or into Control Group, which assesses the effects of standard guidelines, which are verbally provided. Two important moments will be considered to evaluate the results of the intervention (P1, and F1). The primary outcome includes reduced anxiety and the secondary outcome refers to the caregivers’ acquisition of knowledge about chemotherapy treatment.

**Expected results:**

The results of this randomized clinical trial will have a positive impact on the participants’ knowledge acquisition, and will also contribute to reduce anxiety observed at the beginning of treatment related to the caregivers’ knowledge deficit. The level of knowledge between groups with anxiety before and after intervention will be compared, highlighting which intervention had the best effect.

**Evaluation record:**

Registration: RBR-4wdm8q9–Brazilian Registry of Clinical Trials–REBEC (23/03/2022). This study was approved by the Research Ethics Committee of the Federal University of Rio Grande do Norte- UFRN, under CAAE—52597121.9.0000.5537.

## Introduction

Childhood cancer (from 0 to 19 years of age) represents a public health problem, affecting approximately 300,000 new children worldwide each year, with greater increase in developing countries. Furthermore, the World Health Organization (2022) estimates a prevalence of childhood cancer of approximately 600,000 cases worldwide, with leukemia, central nervous system tumors and non-Hodgkin’s lymphoma being pointed out as the most frequent [1].

It is noteworthy that childhood cancer presents a different behavior if compared to cancer in adults, being marked by uncertain mutations and non-evidenced risk factors, making it a challenge for the scientific community mainly related to early diagnosis and treatment [2, 3].

In this context, in relation to treatment, chemotherapy is the basis for therapy, and can be performed alone or associated with surgery and radiotherapy, considerably contributing to improve the prognosis and survival of patients [4].

However, chemotherapy treatment causes the development of negative feelings such as fear and anxiety among parents or caregivers, mainly related to the stigma of the disease, such as not knowing the therapy, its effects and the purpose of treatment [5].

Furthermore, it is in the impact of the diagnosis and definition of treatment that these feelings emerge, consisting a difficult period for the assimilation of information verbally transmitted by health professionals to caregivers. When information is transmitted in an accumulated way and with the use of technical language, caregivers /parents experience greater tension and lack of understanding about the disease and treatment [6, 7].

It is necessary to take into account that the caregiver may not have sufficient schooling to understand technical terms, and it is necessary to facilitate communication using language accessible to all, which should be enlightening, simple and objective [8].

Thus, the guidelines provided to caregivers / parents of children / adolescents undergoing chemotherapy are part of the activities of health professionals and among them the nurse, who plays an essential role in the health education process. Basic care with food, hygiene, hydration and management of chemotherapy side effects constitute important standard guidelines for caregivers and are provided by health professionals [9, 10].

In this context, the use of educational technologies that allow the insertion of resources that can contribute to the strengthening of health guidelines is highlighted. Therefore, the nurse, as an educator and care coordinator, must be on the developing team and use their knowledge and expertise of care in working with the team that develops these resources [11, 12].

Among tools included in the Educational Technology that can be used for the health education process are multimedia strategies, which represent a set of resources that stimulate all the senses, especially vision and hearing. Digital information can be transmitted through audio, video and animation simultaneously [13].

It is noteworthy that health education using multimedia before invasive procedures has shown significant results [14, 15], as an example, a randomized clinical trial that evaluated the effect of an educational video applied before the puncture procedure for intrathecal chemotherapy, demonstrated that the levels of palpitation, fear, dizziness and sweating were reduced in caregivers who watched the educational video before the procedure [8].

Thus, it is believed that the use of a multimedia strategy before chemotherapy administration can contribute to reducing the level of anxiety and prepare the caregiver for the management of children and adolescents undergoing chemotherapy. Based on the above, the study is justified due to the need to investigate the effectiveness of strategies aimed at supporting caregivers during cancer treatment. Furthermore, there are still few interventions using educational technologies for caregivers of children undergoing chemotherapy [16, 17].

Thus, the aim of this study was to evaluate the effect of a multimedia strategy compared to standard guidelines for acquiring knowledge and reducing the level of anxiety of caregivers of children and adolescents with cancer undergoing chemotherapy.

## Materials and methods

This protocol will adhere to the Consolidated Standards of Reporting Trials (CONSORT) [18] and Standard Protocol Items for Randomized Trials statements [19].

### Trial design

This is a protocol for a randomized, two-arm, controlled, interventional clinical trial with single-blind design that evaluated the effect of the multimedia strategy used as a tool for health education in the experimental group (EG) of caregivers, comparing it with the effects of instructions verbally, here called “standard guidelines”, provided to the control group (CG) of caregivers. Both interventions are related to children and adolescents with cancer undergoing chemotherapy treatment.

### Study scenario

Recruitment and intervention will be carried out at the largest philanthropic pediatric hospital that is a reference in the care of children and adolescents with cancer, located in the city of Natal, state of Rio Grande do Norte, Brazil.

### Study population

Caregivers of children and adolescents diagnosed with some type of cancer who will start chemotherapy treatment.

### Sample size

The sample is probabilistic and simple random. Sample size calculation was performed using the G Power software, version 3.1.9.2 (available at: http://www.gpower.hhu.de/). The calculation was performed considering the study by Bernardi et al. [20] that evaluated the IDATE score in caregivers of children and adolescents with cancer. Thus, considering the Cohen effect size of 0.80, test power of 0.80 and significance level of 5% (p-value < 0.05), the study had 26 participants in the Control Group (CG) and 26 participants in the Experimental Group (EG), totaling a sample of 52 study participants.

### Eligibility criteria

Caregivers of both sexes, aged 18 years or older, who are the main caregivers of the children or adolescent with cancer who will start treatment chemotherapy in the ward will be included.

Participants who present the following conditions will be excluded from the study: disorder that prevents understanding and participation in the research; caregivers of children and adolescents who are starting chemotherapy treatment with disease recurrence; caregivers who have already had experience in caring for patients undergoing chemotherapy, individuals with visual or hearing deficits; caregivers of children and adolescents undergoing outpatient chemotherapy.

### Recruitment

Caregivers will be recruited upon admission of the child/adolescent to the pediatric oncology sector of the hospital where the study will be carried out. Caregivers will be contacted and the eligibility criteria for participation in the research will be applied.

Subsequently, the study, interventions and instruments used for data collection will be presented to recruited participants and any doubts that may arise about the study will be addressed. Thus, participants who agree to participate in the study will receive a consent form for reading and signing. The study explanation and the free and informed consent form will be provided by the main researcher. It is noteworthy that participants will have their personal data protected.

### Allocation

The randomization of participants will be carried out through the www.randomizer.org website, which will previously select participants for each group (CG and EG) by simple randomness and without the influence of researchers. The site generates a list with the sequence of participants equally divided into the two intervention groups. It is noteworthy that the allocation of participants will be carried out by a researcher who is not involved in the intervention. Additionally, the allocation will be hidden.

It is noteworthy that randomization will avoid participant selection bias and will allow groups to be compared in terms of their known and unknown risk factors.

### Initial assessment

Participants who accept to participate in the research after signing the free and informed consent form will be presented to the study, interventions, instruments used for data collection and any doubts about the research will be cleared before intervention. After this step, participants will assigned one of two groups (CG and EG) according to the randomization list generated prior to the initial assessment.

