### Intervention

The intervention that will be used in EG is the application of a multimedia strategy associated with the Institution’s standard guidelines. The multimedia strategy is the exhibition of a digital animation film with duration of 12 minutes and 22 seconds addressing the pediatric chemotherapy treatment process.

The film is an educational technology developed by Pinheiro et al. [21], during the master’s degree of the main author, using as reference a manual of a service of Hematology and Oncology of the University Hospital of Santa Maria (HUSM), specialized in the treatment of childhood cancer in partnership with students and professors of the Design, Digital Games and Journalism courses at the Franciscan University (UFN). It was validated by experts in the field and by the target audience and authorized to carry out the study, but it is not available for free access.

The digitally animated film will be shown in a quiet room, before starting chemotherapy. The caregiver will be provided with a headset and a tablet to watch the movie.

The digital animation film used in the study generally addresses the concept of chemotherapy, chemotherapy administration routes, most frequent side effects and general care during treatment. The film emphasizes health education about chemotherapy for the caregiver.

GC will receive instructions verbally. The standard verbal instructions are provided as supplementary material.

The intervention period will be carried out in two days consisting of three stages: the first stage is performed on the first day of contact after admission of the child/adolescent to the chemotherapy unit with the caregiver who, after accepting and signing the informed consent form, will be included in the search.

The second stage is performed on the second day of contact, which will be on the child’s first day of chemotherapy, and before starting the procedure, the main researcher will apply the instrument to assess the level of anxiety (State Trait Anxiety Inventory—STAI) of caregivers in both groups (CG and EG).

Subsequently, the intervention will be carried out according to the groups formed, in which the principal investigator will carry out health education using the multimedia strategy associated with the standard guidelines in the EG and standard guidelines in the CG.

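### As written, group assignment falls after the Day 1 consent step and before the Day 2 baseline STAI; allocation should be released only after the ward start is confirmed and the baseline is taken

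*Protocol article*

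**What the plan says.** All references are to the protocol article.

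- **Recruitment:** eligibility is applied at contact on admission. The study is then explained and consent obtained by the main researcher.
- **Initial assessment:** after consent the study is presented and "any doubts about the research will be cleared before intervention". Then: "After this step, participants will assigned one of two groups (CG and EG) according to the randomization list". The list already exists by then. No day is given for the assignment.
- **Intervention, first stage:** "the first stage is performed on the first day of contact after admission of the child/adolescent to the chemotherapy unit", ending in consent and inclusion.
- **Intervention, second stage:** "The second stage is performed on the second day of contact, which will be on the child’s first day of chemotherapy". The main researcher takes the baseline STAI in both groups. "Subsequently, the intervention will be carried out according to the groups formed".
- **Eligibility criteria:** caregivers of a child "who will start treatment chemotherapy in the ward will be included"; among the exclusions are "caregivers of children and adolescents undergoing outpatient chemotherapy".
- **Allocation:** a list divided equally between the arms, with assignment by a researcher who takes no part in the intervention, and concealment stated.
- **Management of losses and dropouts:** losses are recorded, and a participant who withdraws is taken out of the sample and replaced.
- **Blinding:** covers the post-intervention assessor and the data analysts.

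**The concern.** Nothing specific to an arm happens before the second-day session, so assigning earlier gains nothing. It carries two risks.

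**Randomised caregivers with no data.** The ward-start and outpatient criteria look ahead. They are applied at admission, and the article describes no re-check on the day chemotherapy begins. A caregiver assigned after consent whose child then does not start in the ward has an arm but no baseline STAI, no session and no assessment 30 minutes later. The article has no explicit rule for this case.

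**Arm knowledge at baseline.** The before-and-after STAI comparison is the primary outcome. The baseline half is an interview in which questions are clarified for the caregiver, taken by the main researcher. I read the principal investigator who delivers the session as the same person. If the groups already exist, nothing in the article says that this person is unaware of the arm during the interview, or while deciding whether the caregiver still proceeds.

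**Working it through.** **1. Order of steps.** Set side by side, the sections give:

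| Step | Day | Section |
|---|---|---|
| Eligibility check, explanation, consent | First day of contact | Recruitment; Intervention |
| Assignment from the list | Not named; after consent and clearing of doubts | Initial assessment |
| Baseline STAI, in both groups | First chemotherapy day | Intervention |
| Session, by groups already formed | First chemotherapy day | Intervention |
| STAI and KAI, 30 minutes after the session | First chemotherapy day | Intervention |

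The second stage is described as baseline STAI and then education, with no allocation step between them. The baseline is described as taken in both groups. Assignment therefore precedes the baseline on the natural reading. That it happens on Day 1 itself is an inference: the morning of Day 2 would also fit the wording.

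**2. The plan's own figure.** Inputs from Sample size: d = 0.80, power 0.80, alpha 0.05. For a two-sided, two-sample t-test with n per arm, the noncentrality is d × √(n/2) with 2n − 2 degrees of freedom. Solving for power 0.80 gives n = 25.52, rounded up to 26 per arm and 52 in total. At n = 26 the noncentrality is 0.80 × √13 = 2.88 and power is 0.807. The stated 52 is reproduced, and it contains no allowance for loss.

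**3. Cost if such caregivers stay among the 52 without data.** The article gives no rate of postponement or transfer. The rates below are assumptions, applied equally to both arms; evaluable = 52 × (1 − rate).

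| Assumed loss | Expected lost | Evaluable | Power |
|---|---|---|---|
| 0% | 0 | 52 | 0.807 |
| 5% | 2.6 | 49.4 | 0.786 |
| 10% | 5.2 | 46.8 | 0.763 |
| 15% | 7.8 | 44.2 | 0.738 |
| 20% | 10.4 | 41.6 | 0.711 |

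**4. Cost if the withdrawal rule is extended to them.** The analysed number stays near 52 and the table above does not apply. Instead, people already randomised are deleted, and the equally divided list no longer describes those analysed. A replacement either takes a further list position, which can upset the 26 to 26 split, or fills the vacated arm, which makes that assignment predictable to anyone who knows which arm lost a member.

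**5. With assignment after the baseline.** The sample size is unchanged at 52. Caregivers whose child does not start in the ward are never randomised, so neither cost arises. The remaining window for loss is the session plus 30 minutes.

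**The case against.** The strongest reply is that the article names no day. The assignment sentence only places allocation between consent and the session, Fig 1 was not available for this review, and a condensed article may leave the exact moment to the full protocol. This stands as far as Day 1 is concerned: a reader might infer that assignment is fixed a full day before the start of treatment, and the text does not say so. It does not remove the point, because the wording still places groups before the baseline STAI.

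Three further objections also limit the point:

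- **Postponement may cause no loss.** The second contact is tied to the child's first chemotherapy day, so a late start may only move it. The Fig 1 legend also describes the admission as being for starting chemotherapy. The documents do not support the inference that delayed or transferred children are common.
- **Disclosure of the arm is not stated.** Allocation is said to be hidden and is done by an uninvolved researcher. A reader might infer that the person delivering the session knows the arm from Day 1; no section says so. If the arm is not disclosed, loss caused by the child's course before any session should be unrelated to arm and would cost precision, not validity. What remains is that concealment is stated for the allocation itself, and no section says the baseline interviewer is blind.
- **Replacement keeps the number.** This is correct if the rule is extended. But literally the rule covers withdrawal only, and extending it swaps a small loss of power for exclusion after randomisation.

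**Conclusion.** The point holds as a matter of sequence. As written, assignment comes after consent and before the second-day baseline STAI. This permits randomised caregivers with no data and no explicit rule for handling them, and leaves open whether the baseline of the primary outcome is taken with the arm known.

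Its size cannot be fixed from the article. Under an assumed loss of 5% to 10% without replacement, power is 0.786 to 0.763 against 0.807 as planned, which is modest. With replacement the number holds, and the cost is post-randomisation exclusion. Neither a shortfall in the 52 nor actual bias is shown. The change is worth making because it removes both risks at almost no cost, not because serious harm has been demonstrated.

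**What to change.** State the moment of assignment and reorder the existing steps:

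1. On Day 1, screen and obtain consent, and do not assign.
2. On the child's first chemotherapy day, confirm that the start is in the ward, re-check the eligibility criteria and take the baseline STAI.
3. Only then have the uninvolved researcher release the next allocation, immediately before the session.
4. Record caregivers lost before that point as screened and consented but not randomised. They use no list position and need no replacement.

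Align the Initial assessment and Intervention sections, and the schedule in Fig 1, with this order.

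**Cost:** the allocating researcher must be reachable on Day 2. No visit, staff member or participant is added, the sample size stays at 52, and the child's treatment is not affected.

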### Intervention

The intervention that will be used in EG is the application of a multimedia strategy associated with the Institution’s standard guidelines. The multimedia strategy is the exhibition of a digital animation film with duration of 12 minutes and 22 seconds addressing the pediatric chemotherapy treatment process.

The film is an educational technology developed by Pinheiro et al. [21], during the master’s degree of the main author, using as reference a manual of a service of Hematology and Oncology of the University Hospital of Santa Maria (HUSM), specialized in the treatment of childhood cancer in partnership with students and professors of the Design, Digital Games and Journalism courses at the Franciscan University (UFN). It was validated by experts in the field and by the target audience and authorized to carry out the study, but it is not available for free access.

The digitally animated film will be shown in a quiet room, before starting chemotherapy. The caregiver will be provided with a headset and a tablet to watch the movie.

The digital animation film used in the study generally addresses the concept of chemotherapy, chemotherapy administration routes, most frequent side effects and general care during treatment. The film emphasizes health education about chemotherapy for the caregiver.

GC will receive instructions verbally. The standard verbal instructions are provided as supplementary material.

The intervention period will be carried out in two days consisting of three stages: the first stage is performed on the first day of contact after admission of the child/adolescent to the chemotherapy unit with the caregiver who, after accepting and signing the informed consent form, will be included in the search.

The second stage is performed on the second day of contact, which will be on the child’s first day of chemotherapy, and before starting the procedure, the main researcher will apply the instrument to assess the level of anxiety (State Trait Anxiety Inventory—STAI) of caregivers in both groups (CG and EG).

Subsequently, the intervention will be carried out according to the groups formed, in which the principal investigator will carry out health education using the multimedia strategy associated with the standard guidelines in the EG and standard guidelines in the CG.

The third stage will be carried out on the second day 30 minutes after the end of interventions in which a second researcher, trained to apply the STAI and KAI and who has no understanding of patient allocation, will apply these instruments to participants of both groups, CG and EG.

A pilot test will be carried out with the first nine participants, which will serve for research analysis in order to adapt instruments and the methodological approach as necessary to meet the objectives, for better adherence to the intervention protocol.

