### Data collection instrument

Two instruments will be used for data collection:

State Trait Anxiety Inventory (STAI) [22], an instrument that assesses trait and state anxiety, the first relates to the caregiver’s usual anxiety and the second concerns transient anxiety related to some stressful event. Thus, the aim was to obtain the level of anxiety of participants before and after intervention, comparing these values to evaluate the management of anxiety by intervention, as well as comparing values between groups, evaluating the best management.Knowledge Assessment Instrument (KAI), adapted from the study by Oliveira, Souza and Pellanda [23], which has the aim of assessing the effectiveness of the multimedia strategy used in the acquisition of knowledge by participants.

This instrument has a semi-structured questionnaire composed of three stages: the first consists of sociodemographic data of participants; the second contains information about previous guidelines by other professionals and the participant’s opinion about the intervention performed in order to report whether the intervention was able to resolve doubts about the chemotherapy procedure. The third stage consists of nine questions about the chemotherapy process, to quantify the knowledge that participants obtained on the subject after intervention. The STAI and KAI are validated and reliable instruments used in studies with adults and caregivers [22, 23].

The KAI and STAI instruments will be applied as an interview, clarifying the instrument’s questions and marking the alternative chosen by the research participant. It should be noted that STAI was translated and validated into Portuguese by Biaggio, Natalício and Spielberge [22].

The Knowledge Assessment Instrument (IAC) is a form prepared by the main researcher based on the questionnaire used in the study by Oliveira, Souza and Pellanda (2016) in portuguese.

Fig 1 shows the detailed steps of the study, with SPIRIT schedule of enrollment, interventions and assessments:

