### Primary outcomes

The primary outcome includes reduction in the level of anxiety of caregivers of children and adolescents undergoing chemotherapy. The before and after STAI anxiety data will provide the levels of anxiety of CG and EG to evaluate which intervention had the best effect.

Furthermore, data obtained on participants’ level of anxiety can be used to compare levels before and after intervention of each participant, whether in CG or EG; levels of anxiety between groups before and after intervention, assessing the management of anxiety according to the intervention performed.

STAI response possibilities range from 1 to 4, where: 1 = almost never; 2 = sometimes; 3 = often; and 4 = almost always. The final STAI score is directed to the level of anxiety classified as 20 to 40 points–low level; 41 to 60 points–moderate level; 61 to 80 points–high level.

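### Before and after STAI interviews are taken by different researchers, so the planned within-arm change includes any interviewer difference; the randomised comparison is not biased by a shift common to both arms

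*Protocol article*

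**What the plan says.** The Intervention section of the protocol article sets out the second day in order. Before chemotherapy starts, "the main researcher will apply the instrument to assess the level of anxiety (State Trait Anxiety Inventory—STAI) of caregivers in both groups". The education follows: "the principal investigator will carry out health education using the multimedia strategy associated with the standard guidelines in the EG and standard guidelines in the" control group. The after-assessment comes last: "The third stage will be carried out on the second day 30 minutes after the end of interventions". For this step the protocol names a different interviewer: "a second researcher, trained to apply the STAI and KAI and who has no understanding of patient allocation, will apply these instruments to participants of" each arm. The Blinding section repeats that the after-intervention assessment belongs to this second researcher, who does not know the group.

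The Data collection instrument section fixes how the scores are obtained: "The KAI and STAI instruments will be applied as an interview, clarifying the instrument’s questions and marking the alternative chosen by the research participant". The same section says that the aim is to "obtain the level of anxiety of participants before and after intervention, comparing these values to evaluate the management of anxiety by intervention", and adds a comparison between groups. Primary outcomes defines the outcome as a reduction in anxiety, and states that "data obtained on participants’ level of anxiety can be used to compare levels before and after intervention of each participant, whether in CG or EG".

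**The concern.** The interviewer explains the items and records the answer, and so has some part in the measurement. One person takes all the before-scores and another takes all the after-scores. No caregiver has the same interviewer twice, and no caregiver has the two in reverse order. Within an arm, the data hold nothing that could separate a change in anxiety from a change in how caregivers answer a different person.

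The two interviewers also meet the caregiver in different circumstances. Under Recruitment, the main researcher explains the study and the consent form, so the caregiver already knows that person at the before-interview. The text describes no contact with the second researcher before the after-interview. It says that the second researcher is trained, and mentions no calibration between the two.

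At stake are the statements the protocol intends to make about the fall in anxiety within each arm and each caregiver. They could be too large or too small by whatever the interviewers differ. This is separate from blinding: it would remain if both interviewers were unaware of the arm.

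**Working it through.** **1. The plan's own figure.** Sample size gives a Cohen effect size of 0.80, power 0.80 and a 5% level, with 26 per group. For a two-sided two-sample t-test the noncentrality is 0.80 × √(n/2).
- n = 25: noncentrality 2.828, 48 df, power 0.791.
- n = 26: noncentrality 2.884, 50 df, power 0.807.

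The smallest n that reaches 0.80 is 26, so the stated 52 reproduces. It is a between-arm calculation, and nothing below changes it.

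**2. Where an interviewer difference goes.** Write caregiver i's change (after minus before) in arm g as

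D = τ_g + π + δ + u_i + e_i

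Here τ_g is the effect of the education in arm g, π is time and repeat testing, δ is the average difference between the second and the main researcher's interviews, u_i is the caregiver-specific part of that difference, and e_i is other variation.
- Mean change within an arm estimates τ_g + π + δ. The three cannot be separated, because the interviewer always switches.
- The between-arm difference in mean change estimates τ_EG − τ_CG. Both π and δ cancel if they are the same in both arms. The u_i average to zero in expectation, but add 2 × Var(u)/26 to the variance of the difference.
- The between-arm difference in after-scores uses only the second researcher's interviews, so the switch does not enter it.

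**3. Illustration for a within-arm test.** Inputs:
- From the document: n = 26 per arm and the 5% level.
- Assumed, because the document gives none: STAI SD 10 at both times, before-after correlation r of 0.5 to 0.7, no true change, and a constant shift of 0, 2 or 3 points.
- Also assumed: a paired t-test, which Data analysis does not name.

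The SD of change is 10 × √(2(1 − r)), which is 10.0 at r = 0.5 and 7.75 at r = 0.7. The noncentrality is shift × √26 / SD of change. The critical value is 2.060 on 25 df.

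| Shift | Noncentrality, r = 0.5 | Rejection, r = 0.5 | Noncentrality, r = 0.7 | Rejection, r = 0.7 |
|---|---|---|---|---|
| 0 points | 0 | 5% | 0 | 5% |
| 2 points | 1.020 | 16.5% | 1.317 | 24.5% (0.2446) |
| 3 points | 1.530 | 31.3% | 1.975 | 47.6% |

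**4. Cross-check by simulation.** In 40,000 simulated trials per scenario, with 26 per arm, no true effect and the same shift in both arms, the within-arm paired test rejected in 16.6% (r = 0.5) and 24.1% (r = 0.7) at 0.2 SD. At 0.3 SD it rejected in 30.8% and 47.9%. The between-arm t-test, on change or on after-scores, rejected in 4.7% to 5.2% in every scenario, including those with a shift.

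**The case against.** The strongest reply is that the trial asks a between-arm question. The Objective compares the multimedia strategy with standard guidelines, the sample size is for two groups, and the tests that Data analysis names for the STAI compare intervention with control. In that comparison a shift common to both arms cancels. This stands. A reader might infer from the interviewer switch that the trial's test of the film is biased, but the document does not support that: the switch is the same in both arms, and the blinded second assessor is a strength for the after-scores.

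The within-participant comparison is introduced as something the data can be used for, and no paired test is named. That also stands, and it makes the rejection rates above illustrative. It does not make the comparison absent: Data collection instrument and Primary outcomes both state it, the former as an aim.

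Nothing in the document shows that an interviewer difference exists. The caregiver chooses among fixed answers from 1 to 4, the second researcher is trained, and the pilot in the first nine participants allows the approach to be adapted. A negligible shift is possible, and then the error rate is 5%. Clarifying questions still leaves room for influence, of unknown size and direction.

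Finally, one interviewer would not make within-arm change a causal estimate, since time and repeat testing remain. This is correct. Those components come with any before-after comparison, whereas the interviewer switch is an extra one that can be avoided.

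A reader might also infer that the main researcher knows the arm at the before-interview. The text does not settle this, and the point here does not depend on it.

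**Conclusion.** The point holds within a limited scope, as a cheap improvement. Interviewer and time point are fully aligned by design, and the interviewer takes an active part in the STAI. The within-participant and within-arm changes that the protocol plans to examine therefore include any difference between the two researchers, and no analysis of these data can remove it from a single arm's change.

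The randomised comparison is not biased by a shift common to both arms. The remaining cost there is some added noise if change scores are compared and interviewers differ more for some caregivers than for others; this has not been quantified. The stated 52 participants are unaffected.

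How far within-arm conclusions could be wrong cannot be established from the document. The range from 5% with no shift to 48% with a 3-point shift rests wholly on the assumed SD, correlation, shift and paired test. It shows sensitivity and is not a forecast.

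**What to change.** In the second stage of the Intervention section, have the second researcher, who is already trained in the STAI, apply the before-STAI on Day 2. That person leaves before the education starts and applies the STAI again at F1, still unaware of the arm. Each caregiver then has one interviewer at both times and the after-assessment stays blinded. The Blinding section should state the arrangement.

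The change needs no extra staff, visit or instrument, and the sample size stays as it is. Its cost is scheduling: the second researcher must be available before the education as well as 30 minutes after it, and must be kept away in between. Study status says that recruitment is still being prepared, so the change can be made before data are collected.

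Also add a sentence that within-arm change is descriptive, because it reflects time and repeat testing even with a single interviewer, and that conclusions on the film's effect rest on the between-arm comparison.
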